### Qualitative data analysis

Using a realist evaluation approach to analysis, we will iteratively generate context-mechanism-outcome configurations (CMOc) to clarify what works for whom, why, when and in what context at the individual and practice level [29]. A framework analysis approach will allow us to identify relationships and patterns across diverse data sources, including transcripts, documents, diary entries and observations. Framework analysis has been widely used in health research [40, 41]. Importantly, when using nested case studies as we are, framework analysis facilitates an ordered and organised way to compare and contrast data both across multiple cases and within individual cases.

We will use the seven-step process proposed by Gale et al. [42] to undertake the framework analysis. These steps are 1) transcription; 2) familiarisation; 3) coding; 4) developing a working analytical framework; 5) applying the framework; 6) charting the data; and 7) interpreting the data. By taking this approach we will be able to develop clusters of themes that facilitate both explanatory and descriptive conclusions directly relevant to our case study approach. Case study analysis calls for early analysis and organisation of data, and coding is one way to do this. We will utilise NVivo for Teams for coding and management of the qualitative data sets [43].

### Health economic evaluation

The payment model has been designed following the net benefit correspondence theorem (NBCT) [17–19, 44] to create continuous quality of care improvement incentives with a conservatively health system budget neutral mechanism; with quality of care incentive payments relative to expected downstream cost savings from improved quality. The NBCT provides a generalised method to enable appropriate incentives for improving health system performance, which, as in hospital applications [17, 19], has robust coverage and comparability conditions to create appropriate accountability and prevent perverse incentives - cost and effect shifting and cream skimming.

Importantly, as quality improvement incentives are conservatively budget neutral or potentially somewhat cost saving to the health system, if the trial finds they are effective in improving quality of care relative to usual care, the mechanisms design provides for strong policy-relevant integration into current practice in a health system budget-constrained environment.

Generalisability, implementation and scalability of any such trial findings from case control analysis will be aided by triangulation with qualitative research and pre-post analysis of impacts in the intervention arm, with particular consideration of barriers and enablers to study findings.

The health economic analysis of trial outcomes will jointly consider the health effects and net costs, including downstream health system (prescribed medication and hospital) costs of a capitation-based GP payment system, where bonus payments are continuous across specified ranges for quality of care measures for each of the activities proposed [17–19, 45].

Analysis with patient level data will include representing joint cost and effect distributions on the cost-effectiveness plane (two strategy comparisons), cost-disutility plane (multiple strategy comparisons) and relevant summary measures. These summary measures include internationally recognised best practice measures of the level of the probability of, and expected gain from, being cost-effective: net benefit and cost-effectiveness acceptability curves for two strategy comparison [46]; expected net loss curves and frontiers for multiple strategy comparisons [17, 18, 45], and expected net loss planes and surfaces with multiple domain of effect comparisons [17, 44].

### Sample size and power

To reduce bias and cross-group contamination, we propose to recruit 36 practices and then randomise practices to intervention and control groups of equal sizes. A total of 1800 patients (50 patients per practice) will then be recruited according to identical inclusion and exclusion criteria. The sample size will allow us to detect a change of 0.2 in the mean score of PCAT relational continuity scale (out of a total maximum of 4.0) with 98% power for adult participants, assuming an intracluster correlation coefficient (ICC) of 0.05 at the practice level. The study is powered to detect a similar change in the other domains of the PCAT [47].

In addition, the trial is powered to detect a 40% reduction in PAHs in the 5 years following the trial in comparison with the 12 months prior to the trial in an adult high-risk population with 80% power, assuming an annual PAH rate of 7.5%, ICC of 0.02, attrition of four practices and 25% attrition of patients from remaining practices. Due to funding and time constraints, it is not possible to adequately power the trial to measure a reduction in PAHs within the study period. Therefore, the study investigators will establish data collection procedures to enable ongoing data collection and analysis for up to 5 years.

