### Intervention

Intervention general practices will be supported to implement a new service model incorporating quality incentives for patients’ relational continuity and timely access. The intervention itself will comprise a mechanism of, firstly, patient enrolment within a practice. The practice will then offer enrolled patients: a) guaranteed access to a minimum of three longer appointment types over the study period for older patients or those with chronic or complex illness; b) a review visit within 7 days of admission to an emergency department or hospital, or after other significant health events; and c) for patients aged less than 16 years, same day access for acute conditions.

Figure 2 summarises the incentive structure. All incentives are calculated over the 12 months of the trial and compared with the 12-month period immediately previous to the trial. The incentive payments apply to the percentage of change achieved across the group of enrolled patients at the level of the practice. The incentives supplement the existing payment arrangements. All incentives will be calculated and paid at the conclusion of the 12-month trial.

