Patient	EQ-5D-5 L baseline^c^	IV	Patient self-completion
	EQ-5D-5 L trial completion^c^	DV	Patient self-completion
	PCAT baseline (primary outcome measure)	IV	Patient self-completion [29]
	PCAT trial completion (primary outcome measure)	DV	Patient self-completion [29]
	Hospitalisations previous 12 months (emergency department [ED] + admission)	IV	Patient self-completion
	Hospitalisations during the trial (ED + admission)	DV	Patient self-completion
	Same day consultations <16 years previous 12 months	IV	Patient self-completion
	Same day consultations <16 years during the trial	DV	Patient self-completion
	1 week post-hospital consultations previous 12 months	IV	Patient self-completion
	1 week post-hospital consultations during the trial	DV	Patient self-completion
	DOB	IV	Electronic health record (EHR)
	Sex	IV	EHR
	Smoker	IV	EHR
	Indigenous	IV	EHR
	Diagnoses	IV	EHR
	Medication list number	IV	EHR
	Prescriptions previous 12 months	IV	EHR
	Prescriptions ordered during the trial	DV	EHR
	Pathology received previous 12 months	IV	EHR
	Pathology received during the trial	DV	EHR
	Imaging received previous 12 months	IV	EHR
	Imaging received during the trial	DV	EHR
	Chief diagnoses	IV	EHR
	Time from hospital discharge to appointment	IV	EHR
	Time from request for same day appointment (< 16 yo) to being seen	IV	EHR
	Consultation number	IV	EHR
	Consultation time length	IV	EHR
	Hospitalisations previous 12 months (ED + admission)	IV	EHR
	Hospitalisation during the trial (ED + admission)	DV	EHR
	Mortality during the trial	DV	EHR
	Hospitalisation previous 12 months (ED + admission)	IV	State hospital data
	Hospitalisation during the trial and 5 years following (ED + admission)	DV	State hospital data
	Prescriptions filled previous 12 months	IV	PBS
	Prescriptions filled during the trial and 5 years following	DV	PBS
	Pathology billed previous 12 months	IV	MBS
	Pathology billed during the trial and 5 years following	DV	MBS
	Imaging billed previous 12 months	IV	MBS
	Imaging billed during the trial and 5 years following	DV	MBS
	Specialist consultations previous 12 months	IV	MBS
	Other specialist consultations during the trial and 5 years following	DV	MBS
	Mortality during the trial and 5 years following	DV	Deaths registry

^a^Canadian Institute for Health Information (CIHI). Measuring Organizational Attributes of Primary Health Care Survey. Available at: https://www.cihi.ca/sites/default/files/info_phc_organize_en.pdf [Accessed 8 January 2019]

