### Quantitative data analysis

Baseline characteristics will be summarised at the collaborating PBRN centre and general practice levels within each trial arm, to provide counts and frequencies for categorical variables and means with standard deviations or medians and ranges for continuous variables, as appropriate. The primary outcome measure is a between-group difference in changes in the domain of relational continuity, as measured in the appropriate scale of the PCAT [34] at completion of the trial in comparison with baseline. Between-group differences in the domains of accessibility, coordination and comprehensive care in participants will also be measured and tested using the relevant domain scales of the PCAT [34]. To account for the potential effects of clustering, we will use hierarchical linear models with random main effects specified at the general practice level. Total prescription counts for the 12 months prior to trial commencement will also be used to control for case-mix across the trial.

Similarly, each of the other specified outcome variables (Table 2) will be statistically analysed using multi-level modelling methods to test for between-group (intervention vs. control) differences in the change in variables over the course of the study period. It is intended that data collection from administrative datasets (MBS, PBS and hospital admissions) will be continued beyond the trial period for 5 years, and analysed similarly. Data will not be excluded on the basis of non-adherence or protocol violation. The mixed models treat the data as missing at random and incorporate partial datasets, and are appropriate for analysis of datasets with missing data.

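### The 80% power for avoidable hospitalisations is stated for a before-after contrast; it fits a between-arm comparison that the sentence does not name

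*Protocol article*

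**What the plan says.** Under Sample size and power, the protocol says the trial can "detect a 40% reduction in PAHs in the 5 years following the trial in comparison with the 12 months prior to the trial". The population and power are given as "in an adult high-risk population with 80% power". The inputs are "assuming an annual PAH rate of 7.5%, ICC of 0.02" and "attrition of four practices and 25% attrition of patients from remaining practices", on a design that will "recruit 36 practices and then randomise practices to intervention and control groups of equal sizes". The same paragraph concedes that power for this outcome is inadequate within the study period.

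Under Quantitative data analysis, outcomes other than the primary are to be analysed by multilevel models that "test for between-group (intervention vs. control) differences in the change in variables over the course of the study period", and the 5-year administrative data are to be handled in the same way. Table 3, under Outcomes, lists prior-12-month hospitalisation from state hospital data as an independent variable and "Hospitalisation during the trial and 5 years following (ED + admission") as a dependent variable.

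Under Intervention: "All incentives will be calculated and paid at the conclusion of the 12-month trial".

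**The concern.** The power sentence and the analysis section describe different comparisons. The first sets a later period against an earlier one and mentions no arm. The second is randomised. A before-after contrast absorbs ageing, changes in admission practice and any other trend over 5 years, in either direction, and randomisation does not protect it.

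The two also have different power. A single baseline year in about 360 adults yields only 27 events, and any comparison that subtracts or divides by that year carries its noise. A post-allocation comparison of the arms does not.

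This outcome is the stated reason for setting up linkage for up to 5 years. If the contrast is not fixed before the linked data are seen, a reader cannot tell which test the 80% belongs to, and three readings with widely different power remain open: before-after, difference in change, and baseline-adjusted comparison.

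**Working it through.** **Inputs from the protocol**
- 36 practices less 4 = 32, or 16 per arm if losses are even.
- 50 patients per practice; 120 of the 200 invitation packs go to adults, so about 30 adults per practice. This is an assumption: the adult count is not stated.
- 25% attrition: 30 × 0.75 = 22.5 adults per practice; 16 × 22.5 = 360 per arm.
- Rate 7.5% per year; a 40% reduction gives 4.5%. ICC 0.02.

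**Assumed, because not stated for this calculation:** two-sided alpha 0.05; Poisson counts; within-patient correlation between periods of 0, then up to 0.6.

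**Design effect (DE).** On retained adults: 1 + (22.5 − 1) × 0.02 = 1.43. On planned adults: 1 + (30 − 1) × 0.02 = 1.58. If the practice effect cancels fully within practices: 1.

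**Expected events per arm.** One year before: 360 × 0.075 = 27. Five years after, control: 27 × 5 = 135; intervention: 135 × 0.6 = 81.

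On the log-rate scale, SE = √(DE × Σ 1/events) and power = Φ(|ln 0.6|/SE − 1.96), with |ln 0.6| = 0.511.

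**1. Reproducing the 80%: between arms, 5 years of follow-up**
- Rates, DE 1.43: SE = √(1.43 × (1/135 + 1/81)) = 0.168; power 86%. DE 1.58: SE = 0.177; power 82%.
- Cumulative risk: 1 − 0.925⁵ = 32.3% against 1 − 0.955⁵ = 20.6%. Effective n = 360/1.58 = 228 gives 81%; 360/1.43 = 252 gives 85%.

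So the stated figure is recovered at about 81% to 86%.

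**2. The contrast as written: intervention-arm adults, 5 years after against 12 months before**
- DE 1.58: SE = √(1.58 × (1/27 + 1/81)) = 0.279; power 45%.
- DE 1.43: SE = 0.266; power 49%.
- DE 1: SE = 0.222; power 63%.
- Risk scale (7.5% in one year against a mean annual 4.5% over five): 40% with DE 1.43 and 53% with DE 1 at zero correlation; 58% and 73% at correlation 0.6.

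**3. The analysis section read as an unadjusted change score**
- DE 1.58: SE = √(1.58 × (2/27 + 1/135 + 1/81)) = 0.385; power 26%.
- DE 1.43: SE = 0.366; power 29%.
- DE 1: SE = 0.306; power 39%.
- Risk scale, DE 1.43 or 1, correlations 0 to 0.6: 22% to 46%.

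**4. Window.** If follow-up includes the trial year, as the Table 3 row does, there are 27 × 6 = 162 and 162 × 0.6 = 97 events. With DE 1.43, SE = 0.153 and power is about 91%. The 5-year and 6-year figures are not interchangeable.

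**The case against.** The strongest reply is that the number is right and only the sentence around it is loose. That largely stands: the 80% is recovered from the protocol's own inputs as a between-arm comparison, and Table 3 already lists the prior 12 months as an independent variable, which fits a baseline-adjusted model. Such a model should keep the power of step 1. A reader might infer from step 3 that the planned analysis has about one-third power, or that the trial cannot detect a 40% reduction at 5 years. The documents do not support either. The low figures follow only if the difference in change is an unadjusted change score, and the protocol does not say that it is.

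A second reply is that the before-after figures depend on unstated inputs. This is true. Applying a correlation of 0.6 to the log-rate estimates would give 79% to 91% in step 2. I would not rely on that: if the correlation arises because patients differ in underlying rate, those differences cancel in the before-after ratio and leave Poisson noise of 1/27 + 1/81, which is 63% again. Since no arm is named, pooling adults of both arms is another reading; with 54 and 162 events it gives 78% (DE 1.43) to 90% (DE 1). But control patients receive usual care, so that contrast does not measure an intervention effect.

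Three further inferences should be resisted. Regression to the mean is a weak argument here, because adults qualify by age or chronic diagnosis and not by recent admission. The absence of a separate row for avoidable hospitalisation in Table 3 is not a defect: the outcome is named in the text, and its derivation from hospital data is commonly left to the full protocol or analysis plan. The protocol also gives no figures for a waning effect or for over-dispersion, so no power loss can be attributed to either.

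**Conclusion.** Wrong as written. The power sentence attaches 80% to a contrast that is not the randomised one and that, for intervention-arm adults, gives about 45% to 63% on the log-rate scale with no within-patient correlation, and up to about 73% on the risk scale with a strong one. The 80% belongs to a between-arm comparison over 5 years of follow-up (about 81% to 86%).

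This rests on two-sided alpha 0.05, about 360 retained adults per arm, an even loss of practices, and a design effect of 1.43 or 1.58 for the between-arm figure. A design effect built on all 50 patients per practice (1.98) would bring the cumulative-risk figure down to 72%. If the 40% applies to the cumulative risk itself (32.3% against 19.4%), it rises to 91% with DE 1.43.

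The analysis section adds an ambiguity that matters (about 26% to 39% if run as an unadjusted change score) but not an established shortfall. The outcome is secondary, the primary analysis is untouched, and the protocol is open about low power within the study period. The correction is worth making but is not critical.

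**What to change.** **Sample size and power.** Replace the comparison with the prior 12 months by the randomised contrast: a 40% lower rate (or cumulative risk; choose one) of potentially avoidable hospitalisation in the intervention arm than in the control arm over the 5 years following the trial. State alpha, the number of adults assumed and the design effect used. Say that the 80% assumes the 40% reduction holds on average over those 5 years, since incentives are calculated over the 12-month trial and paid at its end.

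**Quantitative data analysis.** State that the 5-year outcome is compared between arms in a mixed model with a practice random effect, and that the prior-12-month count of potentially avoidable hospitalisations enters as a covariate and is not subtracted.

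**Window.** State whether follow-up starts at the end of the trial or includes the trial year. If it includes the trial year, recompute the power for that window.

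The cost is a few sentences in the protocol and matching text in the analysis plan, with no new data and no change to sample size. It should be settled before the linked outcome data are seen.

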### Trial governance

All Chief Investigators are members of the trial steering committee, which meets every 2 weeks. Its remit includes data management. It is independent from the sponsor. Any reports of potential harm from participating general practices or patients will be investigated by the Steering committee and, if appropriate, reported to the ethics committees.

## Discussion

This trial consists of a practice-based intervention implemented in the primary care setting and predominantly using quantitative data collection and analysis. The trial is designed to test the effects of a new funding model that provides financial incentives for continuous quality improvement in general practice, proportional to the expected downstream cost savings. As part of the trial design, nested case studies are planned. These are intended to contextualise the quantitative findings and provide insights into the attitudes and beliefs of patients and practitioners, and their perceptions about the success or otherwise of the intervention.

The development of the intervention was underpinned by several key tenets, namely that:high-quality primary health care can reduce the use of secondary care, thus reducing health system costs;the design and use of financial models that support high-quality primary care are crucial to the uptake of quality improvement activities and better patient outcomes; andfinancial incentives for quality improvement are more likely to succeed when incentives are continuous and targeted to specific tasks that are closely linked to high-quality care.

Thus, the trial was designed to incentivise GPs to provide enrolled patients with longer consultations, same day access and rapid follow-up after hospitalisation, and to achieve associated quality improvements linked to these tasks. The primary outcome measure of the trial is patient-perceived relational continuity and secondary outcomes include changes in pathology and imaging, total prescriptions and rates of PAHs - all indicators of quality of care.

The design of funding models to support high-quality primary care is crucial to the uptake of quality improvement activities and better patient outcomes [48]. Health economic theory suggests that incentives with GP payments based on fee-for-service can be significantly improved with capitation payments conditional on continual quality improvement [49–54]. Indeed, our review of international financial models for effective primary care indicated that a blend of fee-for-service, capitation and pay-for-performance elements appeared to provide the best balance between improved patient outcomes and productivity. However, the evidence strongly suggested that the incentives were only successful when targeting tasks closely linked to professional standards of high-quality care [48].

The funding model within the trial seeks to provide incentives to encourage:access to a preferred provider, longer consultations and structured follow-up after hospitalisation among older and chronically ill general practice patients;reduced referrals for specified radiology and pathology services, and overall medicine prescriptions for older and chronically ill general practice patients;improved access to same-day care for under 16-year-olds with defined comorbidities; andreduced PAHs and emergency department attendances for all enrolled patients.

It is important to note that the absolute incidence of PAHs in the general population is low at around 2.8% per annum, which means that enrolling a non-selected cohort of patients is likely to lead to a null trial with time and funds available. In the 65–74 years age group, the national rate of PAH for 20011/12 was 7,344.8 per 100,000 population (7.3%). For those aged 75 years and over, the rate was 13.4% [55].

Chronic conditions contribute a significant proportion of PAHs, with diabetes complications, COPD, cardiac failure, asthma and angina being most common [56]. Hence, we have focused on high-risk chronic/complex patients aged 18–65 years with the highest-risk ACSCs (COPD, diabetes, angina, ischaemic heart disease, cardiac failure, asthma) expected to have greatest benefit and health system cost saving where the model of care is effective.

The rate of PAHs in the general population under 16 years of age is approximately 2% per annum [55]. Hence, we have targeted recruitment of patients aged less than 16 years to those with an increased risk of hospitalisation. Research from New Zealand has demonstrated a high rate of re-hospitalisation in under 15-year-olds with a defined expert-derived list of child-specific potentially avoidable hospitalisations (approximately 80% of re-hospitalisations up until 15 years of age) [57]. We are therefore using these diagnoses to recruit participants (includes asthma, epilepsy, acute bronchiolitis, pneumonia, croup and dental conditions).

We are using an embedded mixed methods design to incorporate a qualitative component into an outcomes-based randomised controlled trial. This qualitative data will be used to develop understanding of how the intervention is experienced by participants, and to help contextualise and explain the quantitative results. Our analysis aligns with Creswell and Plano Clark’s model of mixing data using embedded mixed method design [58]. At a pragmatic level, we anticipate that by integrating the embedded qualitative component with our quantitative trial data we will better be able to:reveal and contextualise relationships between variables and outcomes;explore and possibly explain differences in effect size;assess the acceptability of the trial model from multiple perspectives; andprovide insight into discrete, potentially unanticipated impacts of the model on patients and practitioners.

The trial is designed to generate robust, policy-relevant evidence of the impact of a new service model of primary care practice, comprising targeted practice incentives for patient enrolment with a preferred provider, longer consultations, same day access and structured follow-up after hospitalisation, on the quality of primary care and health service utilisation for patients at increased risk of hospitalisation. In addition, the trial will provide evidence on continuous quality improvement incentives which can be compared to block funded pay-for-performance models in the UK [59], the patient-centred medical home model in the United States [60] and the Australian Government ‘Health Care Homes’ trial [31].

